**Anti-COVID19 Vaccination AKS-452X BOOSTER Study (Protocol nr. 901452-CT-21-001)**

---

and costs of the other viral-based, nucleic acid-based, and full-length recombinant SP subunit-based vaccines. The potency, manufacturability, and mechanism-of-action of the AKS-452 Fc-fusion protein formulated with / without adjuvant, resp. primary vaccination and booster vaccine, therefore, offer an opportunity to immunize billions of people globally as frequently as necessary to maintain high levels of neutralizing anti-SP/RBD Ab titers throughout the population, regardless of COVID-19 status; i.e., boosting of those with prior SARS-CoV-2 infection or of those who received a prior vaccination.

**Anti-COVID19 Vaccination AKS-452X BOOSTER Study (Protocol nr. 901452-CT-21-001)****Table 1:** Target product profile (TPP) of the SARS-CoV-2 vaccine, AKS-452: a recombinant human IgG Fc fusion protein with the SARS-CoV-2 spike protein receptor-binding domain (SP/RBD-Fc).

| Item                                              | Desired target                                                                                                                                                                                                                                                                                                                                                                                                                                                                                                                                 |
|---------------------------------------------------|------------------------------------------------------------------------------------------------------------------------------------------------------------------------------------------------------------------------------------------------------------------------------------------------------------------------------------------------------------------------------------------------------------------------------------------------------------------------------------------------------------------------------------------------|
| Drug structure and formulation                    | 
A subunit vaccine comprised of:
 
 
• a human IgG Fc moiety
 
• a linker
 
• a recombinant SP/RBD
 
                                                                                                                                                                                                                                                                                                                                                                           |
| Indications                                       | 
 
• A primary vaccine to protect against lethal infection caused by the SARS-CoV-2 virus
 
• A boosting immunization for anti-SARS-COV-2 SP/RBD Ab positive individuals from prior infection (or immunization) to maintain immunity
 
                                                                                                                                                                                                                                                     |
| Mechanism                                         | 
 
• Induction of SP/RBD-neutralizing antibodies without causing undesired immunopotentialization such as: 
 
○ Th2-type immunopathology, including lung eosinophilia, and/or
 
○ Antibody Dependent Enhancement (ADE) of infectivity
 
 
 
• Fc moiety focuses SP/RBD Ag to immune cells that express Fc receptors in addition to increasing Ag half-life allowing for “extended immune stimulation” to achieve single dosing
 
 |
| Target population                                 | 
 
• Adults >18 years of age
 
• Suitable for adult healthcare workers
 
• At-risk, adults > 65 years old
 
• Individuals with underlying diabetes or hypertension
 
                                                                                                                                                                                                                                                                                                   |
| Route of administration                           | Subcutaneous                                                                                                                                                                                                                                                                                                                                                                                                                                                                                                                                   |
| Product presentation                              | Multi-dose vials; 1.0 mL fill with $\geq 0.8$ mL extractable volume of AKS-452X (concentrated)                                                                                                                                                                                                                                                                                                                                                                                                                                                 |
| Dosage                                            | 
 
• 90 µg of the SP/RBD-Fc antigen.
 
                                                                                                                                                                                                                                                                                                                                                                                                                                                            |
| Booster Dosage schedule                           | 
 
• Maximum of one booster immunization regardless of age <math>\geq 3</math> months after last vaccination dose
 
• Potential booster immunizations no more frequently than every 6 months
 
                                                                                                                                                                                                                                                                                             |
| Warnings and precautions/ pregnancy and lactation | 
 
• Mild-to-moderate local injection site reactions, such as erythema, edema and pain, the character, frequency and severity of which is similar to or slightly less than licensed recombinant protein vaccines.
 
• Less than 0.01% risk of urticaria and other systemic allergic reactions.
 
• Incidence of SAEs no more than licensed comparator vaccines
 
                                                                                                                    |

**Anti-COVID19 Vaccination AKS-452X BOOSTER Study (Protocol nr. 901452-CT-21-001)**

|                      |                                                                                                                                                                |
|----------------------|----------------------------------------------------------------------------------------------------------------------------------------------------------------|
| Expected efficacy    | Minimum of 80% efficacy in inducing protective Ab titers, potentially leading to herd immunity and a significant reduction in SARS-CoV-2 associated infections |
| Co-administration    | All doses may be co-administered with antiviral drugs and/or other vaccines used in public health emergencies.                                                 |
| Storage              | Refrigeration between 2-8°C. Can be out of refrigeration (at temperatures up to 25°C) for up to 2 weeks or longer, based on current stability studies.         |
| Shelf-life           | 12 months at -80°C, currently one month at room temperature upon thaw or one month at 2-8°C upon thaw.                                                         |
| Product registration | Licensure by European regulatory agencies and FDA in the US                                                                                                    |

## 4. STUDY POPULATION

### 4.1 Population (base)

In the phase II ACT-BOOSTER study, healthy volunteers aged 18-85 years old, are recruited for this study.

The study population will be a representation of the general population in terms of characteristics as sex, ethnical background etc.

### 4.2 Inclusion criteria

In order to be eligible to participate in this study, a subject must meet all of the following criteria:

- Age 18-85 years (extremes included), males and females.
- Body mass index (BMI) between 19.0 and 30.0 kg/m^2, inclusive
- General good health, without significant medical illness, as determined via physical exam findings, or vital signs
- No clinically significant laboratory abnormalities as determined by the investigator
  - o Note: one retest of lab tests is allowed within the screening window
- Informed Consent Form signed voluntarily before any study-related procedure is performed, indicating that the subject understands the purpose and procedures required for the study and is willing to participate in the study
- Willing to adhere to the prohibitions and restrictions specified in this protocol
- All participants have received a completed (registered) vaccine at least 3 months before inclusion in this study (i.e. Pfizer [Comirnaty], Moderna [Spikevax], Janssen [Ad26.COV2.S], AstraZeneca [Vaxzevria]).
- Negative hepatitis panel (including hepatitis B surface Ag and anti-hepatitis C virus Abs) and negative human immunodeficiency virus Ab and Ag screens at screening
- Female subjects should fulfil one of the following criteria:
  - o At least 1 year post-menopausal (amenorrhea >12 months)
  - o Surgically sterile (bilateral oophorectomy, hysterectomy, or tubal ligation);
  - o Will use adequate forms of contraceptives from screening to discharge.
- Female subjects of childbearing potential and male subjects who are sexually active with a female partner of childbearing potential must agree to the use of an effective method of birth control from screening to discharge
  - o Note: medically acceptable methods of contraception that may be used by the subject and/or partner include combined oral contraceptive, contraceptive vaginal ring, contraceptive injection, intrauterine device, etonogestrel implant, double barrier, sterilization and vasectomy
- Female subject has a negative pregnancy test at screening and upon check-in at the clinical site.
  - o Note: pregnancy testing will consist of a serum pregnancy test at screening and urine pregnancy tests at the dosing visit, in all women.

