3. Emulsification of SP/RBD-Fc in the water-in-oil adjuvant, Montanide ISA 720 (only primary vaccine – which is not part of the booster vaccine used in this study)

In summary, the Fc moiety on AKS-452 is designed to act as a mild adjuvant via inducing activation signaling to the antigen-presenting cell (APC) via FcγRs to enhance the duration of Ag exposure to APCs and perhaps direct Ag entry into lymph nodes locally and systemically where additional APCs reside. As a consequence, the Fc moiety is expected to create a dramatic dose-sparing potential for both the Ag such that the risk of reactogenicity (a safety concern) is dramatically reduced; i.e., too much adjuvant that over-activates many APCs and other innate immune cells can lead a systemic inflammatory reaction termed *reactogenicity*. Such reactogenicity is induced acutely after injection and is not mediated by T and B cells.

**Aim:** To investigate if a subcutaneous (s.c.) booster dose of 90 µg of the concentrated naked Akston AKS-452 vaccine (AKS-452X) at  $\geq 3$  months post initial vaccination, with any of the four registered vaccines, will boost the antibody titer and immune response in human healthy volunteers 4-6 weeks after s.c. injection.

**Hypothesis:** A booster dose of naked (i.e. non-adjuvanted) AKS-452 vaccine will provide an enhanced immune response after vaccination with any of the registered vaccines against COVID-19.

**Primary objective:** To determine the immunogenicity 4-6 weeks after subcutaneous injection of a booster dose of AKS-452X vaccine given at  $\geq 3$  months post-initial vaccination (i.e. Pfizer [Comirnaty], Moderna [Spikevax], Janssen [Ad26.COV2.S], AstraZeneca [Vaxzevria]) in human healthy volunteers.

**Secondary objective:** Vaccine safety and side effects after booster vaccination. Follow-up will occur for up to 9 months post-study vaccine.

**Study design:** Single center, open-label, safety and efficacy study on the biological activity of a SP/RBD-Fc antigen booster vaccine (AKS-452X) against COVID-19.

**Study population:** Healthy human volunteers, 18 - 85 years, having received a registered vaccine (i.e. Pfizer [Comirnaty], Moderna [Spikevax], Janssen [Ad26.COV2.S], AstraZeneca [Vaxzevria]).

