### 4.3 Exclusion criteria

A potential subject who meets any of the following criteria will be excluded from participation in this study:

- Pregnant or breast-feeding females
- Evidence of clinically significant neurologic, cardiac, pulmonary, hepatic, hematologic, rheumatologic, endocrine, autoimmune, oncologic, or renal disease
- Any laboratory test which is abnormal, and which is deemed by the Investigator(s) to be clinically significant
- Behavioral or cognitive impairment or psychiatric disease that in the opinion of the investigator affects the ability of the subject to understand and cooperate with the study protocol
- Current alcohol/illicit drug/nicotine abuse or addiction: history or evidence of current drug use or addiction (positive drug screen for amphetamines, barbiturates, benzodiazepines, cannabinoids, cocaine, or opiates) or signs of excessive use of alcohol at screening and at day 0.
- Presence of any febrile illness ( $T \geq 38.0^{\circ}\text{C}$  or lab confirmed viral disease (PCR)) or symptoms suggestive of a viral respiratory infection within 1 weeks prior to vaccination. Participants will be screened for SARS-Cov-2 with an EUA-approved PCR test at screening, and at day 0.
- Use of corticosteroids (excluding topical preparations for cutaneous or nasal use) or use of immunosuppressive drugs within 30 days before inoculation
- A history of anaphylaxis, history of allergic reaction to vaccine, known allergy to one of the components in AKS-452X. Mild allergies without angio-edema or treatment need can be included if deemed not to be of clinical significance (including but not limited to allergy to animals or mild seasonal hay fever)
- A history of asthma within the past 10 years, or a current diagnosis of asthma or reactive airway disease associated with exercise
- Receipt of blood or blood-derived products (including immunoglobulin) within 6 months prior to vaccination.
- Receipt of another investigational agent within 30 days or 5 times the product half-life (whichever is longest) prior to vaccination
- Deprived of freedom by an administrative or court order or in an emergency setting
- Any condition that in the opinion of the principal investigator (PI) would jeopardize the safety or rights of a person participating in the trial or would render the person unable to comply with the protocol.

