| 5                | 0.88       | 0.806        | 33      |
| 6                | 0.90       | 0.812        | 26      |
| 7                | 0.92       | 0.802        | 20      |
| 8                | 0.94       | 0.807        | 16      |

**Table 2:** The POWER procedure Z test for binomial proportion

[figure not shown]

**Figure 9.** The POWER procedure Z test for binomial proportion

- If we consider a realistic minimum 80% conversion rate outcome in the phase II ACT-BOOSTER study, each treatment cohort will consist of 119 subjects. Considering a drop-out rate of 20%, this relates to 150 subjects per cohort (totaling 600 subjects). The minimum 80% conversion rate is considered realistic since the one single-dose injection cohort of 90 µg and the two-dose injection of 45 µg each demonstrated a 100% conversion rate in phase I/II.

Based on the above assessment of the statistical analysis, a total of 150 subjects per registered vaccine cohort will be included for the Phase II ACT-BOOSTER study, as this relates to a realistic outcome estimate based on the phase II ACT-study seroconversion rates for a single-dose injection group of 90 µg (26 subjects) and two-dose injection group of 45 µg (26 subjects), totaling 52 participants.

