## 7. METHODS

### 7.1 Study parameters/endpoints

#### 7.1.1 Main study parameter/endpoint

**Main study parameters/endpoints: Primary endpoint:** The percentage of patients that i) achieve an SP/RBD-specific IgG antibody titer level of  $\geq 2.42 \mu\text{g/mL}$  at the day 28 time-point post-intervention (i.e. booster vaccine) if the base-line value prior to receiving the booster vaccine was  $< 2.42 \mu\text{g/mL}$  or ii) where the SP/RBD-specific IgG antibody titer is at least 2x the base-line value prior to receiving the booster vaccine if the base-line value prior to receiving the booster vaccine was  $\geq 2.42 \mu\text{g/mL}$ . The percentage of patients in each of the four cohorts that achieve the primary endpoint threshold at 28 days post-intervention will be calculated (n (%)).

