### 7.2 Randomisation, blinding and treatment allocation

The study is a single-centre, open-label Phase II clinical AKS-452X booster vaccine-evaluation study. No randomisation is applicable, nor blinding. All subjects included will receive the active vaccine AKS-452 without adjuvant. The Phase II study will comprise 150 subjects per cohort (all subjects will receive the active vaccine).

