### 9.3 Primary study parameter(s)

The primary aim of this booster vaccination study is to investigate if a subcutaneous (s.c.) booster dose of 90 µg of the naked Akston AKS-452X vaccine at  $\geq 3$  months post initial vaccination, with any of the four registered vaccines, will boost the antibody titer and immune response in human healthy volunteers 4weeks after s.c. injection.

Safety: Adverse events are defined as any undesirable experience occurring to a subject during the study, whether or not considered related to the investigational product / trial procedure/ the experimental intervention. All adverse events reported spontaneously by the subject or observed by the investigator or his staff will be recorded.

Evaluation of Safety and Tolerability:

Safety and tolerability will be assessed through AEs and clinical laboratory, and any other parameter that is relevant for safety assessment.

Adverse Events: a listing of all individual AEs will be provided. Summary tables of TEAEs will be presented by system organ class based on the MedDRA terminology list (preferred terms): containing the number of TEAEs (frequency of occurrence, number of subjects experiencing the event) by treatment and containing the number of drug-related TEAEs (frequency of occurrence, number of subjects experiencing the event) per treatment. Additional tables of total counts by treatment and relationship and by treatment and severity will be given.

Laboratory data: clinical laboratory data will be listed accompanied by an indication if the parameter is outside the reference range. A summary of all data outside the reference range of the clinical laboratory will be provided. Clinical laboratory data will be presented descriptively, where applicable.

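### The 3-month entry interval is not tied to the last COVID-19 vaccine dose, so a recently re-dosed subject is literally eligible and their response cannot be attributed to AKS-452X

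*Protocol*

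**What the plan says.** Protocol section 4.2 is the rule that admits subjects: "All participants have received a completed (registered) vaccine at least 3 months before inclusion in this study". Other sections use related but different anchors:

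- The Summary (Aim) speaks of at least 3 "months post initial vaccination, with any of the four registered vaccines, will boost the antibody titer".
- Section 9.3 likewise has at least 3 "months post initial vaccination, with any of the four registered vaccines", and section 2.1 also counts from the initial vaccination.
- Section 5.5 refers only to receipt of a registered vaccine 3 or more months ago.
- Table 1, in its booster schedule row, alone counts from the last dose: at least 3 "months after last vaccination dose".

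The nearest exclusion in section 4.3 is "Receipt of another investigational agent within 30 days or 5 times the product half-life". That section also sets intervals for blood products and for corticosteroids or immunosuppressants, but none for a registered COVID-19 vaccine. The schedule in section 7.3 has eligibility checked at screening (Day -28 to -2) and again at Day 0.

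Under section 7.1.1, a subject with a baseline of 2.42 µg/mL or more responds at Day 28 if the "antibody titer is at least 2x the base-line value prior to receiving the booster vaccine". A subject starting below 2.42 µg/mL responds by reaching that value. Section 7.2 states: "No randomisation is applicable, nor blinding". All subjects receive AKS-452X.

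**The concern.** A course completed long ago and a last dose taken recently are compatible, and section 4.2 tests only the first. The protocol itself recognises that registered vaccines may need further boosting (section 1.4) and that third doses are being given elsewhere (section 3). Volunteers are recruited from the general public (section 10.2).

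The primary result is each cohort's percentage of subjects who respond relative to their own Day 0 value. If a registered dose was given shortly before Day 0, it affects the denominator of that ratio, the Day 28 numerator, or both. In an uncontrolled trial nothing separates its effect from that of AKS-452X. A further dose of a different product also blurs which of the four vaccine cohorts the subject belongs to.

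**Working it through.** **Step 1: does any criterion stop a re-dosed subject?** Take a subject whose course ended 8 months before Day 0 and who took another registered dose 3 weeks before Day 0.

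| Protocol text | Result |
|---|---|
| 4.2, completed vaccine at least 3 months ago | Met |
| Summary, 2.1 and 9.3, interval from initial vaccination | Met |
| 5.5, received a registered vaccine 3 or more months ago | Met |
| 4.3, investigational agents | Does not apply to a registered vaccine |
| 4.3, blood products and immunosuppressants | Do not apply |
| 4.3, investigator's judgement | Limited to safety, rights or ability to comply |
| 4.6, co-medication | No restriction |
| Table 1, last dose at least 3 months ago | Not met, but this is a target product profile and does not screen subjects |

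The Day 0 check applies the same criteria, so it does not act on such a dose either, even one taken between screening and Day 0. For a subject with only one course, the completing dose is the last dose, and sections 4.2 and Table 1 agree.

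**Step 2: direction of the bias.** If the extra dose has already raised the Day 0 titer, doubling is harder and the cohort percentage falls. If the titer is still rising at Day 0, the registered dose itself helps the subject reach twice baseline by Day 28, and the percentage rises. The documents do not settle which would dominate.

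**Step 3: the plan's own sample size.** Inputs from section 4.4: null proportion 0.70, alternative 0.80, one-sided alpha 0.05, power 0.80, null variance.

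n = [(1.645·√(0.7·0.3) + 0.842·√(0.8·0.2)) / (0.80 − 0.70)]² = 118.9, so 119. This matches Table 2. With 20% drop-out, 119/0.8 = 148.75, so 149; the protocol enrols 150.

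**Step 4: illustration in both directions.** With N = 119, the z test rejects at 92 or more responders (exact size 0.048). Let g be the share re-dosed and r their response rate. Both are assumptions. With 80% response in the rest, the cohort rate is 0.80(1 − g) + r·g, and the exact binomial probability of 92 or more is:

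| g | r | Cohort rate | Chance of rejecting |
|---|---|---|---|
| 0 | – | 0.800 | 0.804 |
| 2% | 20% | 0.788 | 0.700 |
| 2% | 50% | 0.794 | 0.755 |
| 5% | 20% | 0.770 | 0.519 |
| 5% | 50% | 0.785 | 0.672 |
| 5% | 80% | 0.800 | 0.804 |
| 5% | 95% | 0.8075 | 0.857 |

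The last row is no gain: the added chance of success comes from the other vaccine.

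Section 4.4 treats 80% as a floor ("If we consider a realistic minimum 80% conversion rate outcome"). At 84% in the rest, the chance is 0.979 with no re-dosed subjects. At r = 20% it is 0.950 for a 2% share and 0.860 for a 5% share. The downward effect is therefore large only if the true rate is near 80%.

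**The case against.** The best defence is that the population described has had one registered course, for which section 4.2 is correct. Staff would naturally read a completed vaccine as vaccination finished, and Table 1 confirms that intent. No section says that already re-dosed volunteers are expected. Medical and medication history is taken at screening, so a recent dose may come to light. An analysis plan could set such subjects aside, and each cohort enrols 150 − 119 = 31 above the required number.

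Much of this stands. It limits the number likely to be affected and makes the primary result partly recoverable. It does not close the gap: a recent dose that is discovered still breaches no criterion, and the interval cannot be restored after enrolment. That Table 1 states the intended interval is a reason to put it in section 4.2.

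A reader might infer that the gap necessarily dilutes the response rate and costs power. The documents do not support that, because a titer still rising at Day 0 would push the rate up.

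**Conclusion.** The point holds as a gap in the wording of the entry rule, worth closing because doing so is cheap. As written, section 4.2 admits a subject given a further registered dose within 3 months of Day 0, contrary to the interval in Table 1. For that subject, the response cannot be attributed to AKS-452X.

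The size is unknown. At N = 119, 80% in the rest and an assumed 5% share, the chance of a positive cohort result runs from 0.52 (20% response among the re-dosed) to 0.86 (95%), against 0.80 with none. These are illustrations on assumed inputs. If no re-dosed subject enrols, nothing is lost.

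Two further inferences should be resisted. One is that the 3-month minimum fails in general; it holds for every subject with a single course. The other is that the trial is underpowered; the stated 119 reproduces exactly, and the wording does not change it.

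**What to change.** Amend section 4.2 to require both a completed registered vaccine and at least 3 months between the last dose of any COVID-19 vaccine and Day 0, checked at screening and again at Day 0. Align the wording of the interval in the Summary, section 2.1, section 5.5 and section 9.3.

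The cost is one phrase in the criteria and matching edits in four places. A few volunteers become ineligible. The 119 evaluable and 150 enrolled per cohort stay as they are.
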